## Assignment of interventions: allocations

### Sequence generation {16a}

Families are allocated by simple random sampling into either arm of the study using the platform CSAM MedSciNet Clinical Trial Framework (CSAM). When the CHC-nurse has recruited 10–16 families, 50% of the families will be assigned to the intervention group and 50% to the control group.

### Concealment mechanism {16b}

Use of a validated password website CSAM will ensure concealment.

### Implementation {16c}

When twice the number of families needed for a full parental group have completed baseline questionnaires, the CHC-nurse uses the platform CSAM to randomize the families into the two arms of the study. CSAM performs the randomization without any possibility for the CHC-nurse to intervene. Information about allocation is sent automatically to the families by CSAM after randomization. Links to the digital lectures are included in the email to the control group. Thereafter, the parents in the intervention group receive information about the time and place for the group meetings from the CHC-nurse.

## Assignment of interventions: blinding

### Who will be blinded {17a}

Neither participants nor group leaders are blinded because of the nature of the intervention and for ethical reasons. Everyone is aware of the two groups (Little ACF and digital lectures). Researchers are blinded to intervention allocation (Little ACF or digital session) during statistical analyses of the primary outcome.

### Procedure for unblinding if needed {17b}

Unblinding for researchers will be done in the study after statistical analyses of the primary outcome.

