#### Primary outcome

The primary outcome is five aspects of parenting strategies, measured at all five time points of the study (T1, T2, T3, T4, and T5). Parenting self-efficacy (PSE) [16, 20] is measured with 48 items that are assessed with an 11-point Likert scale from 0 (completely disagree) to 10 (fully agree) using a modified version of *Tool to Measure Parenting Self-Efficacy* (TOPSE) [21].

The emotional regulation of the parent in relation to the child is measured using the *Parent Emotion Regulation Scale* (PERS) developed by Pereira et al. [22]. The PERS consists of 20 questions that are to be answered on a scale from 1 (never or almost never) to 5 (always or almost always). For the purpose of our study, questions nr 1, 11, and 18 were removed based on a validation study of the PERS that took place prior to the study (Manuscript in preparation).

How parents handle children’s negative emotions is assessed using the *Coping with Toddlers’ Negative Emotion Scale* (CTNES) [23]. In its original version, 12 situations are described to which the parents should assess the likelihood of using 6–7 different strategies to solve each situation. The likelihood assessment ranges from 1 (not likely at all) to 7 (very likely). For this study, 8 situations (items 3–10) were selected based on the analysis from the validation of the Swedish version (Manuscript in preparation).

Parental stress is assessed using the scales *incompetency* and *role limitation* from the *Swedish Parenting Stress Questionnaire* (SPSQ) [24]. The items are assessed with 5 response alternatives.

Five questions inspired by the *Coparenting Relationship Scale* [25] are used to assess the quality of parents’ coparenting relationship. The answers range from 1 (not true at all) to 5 (very true) on a 5-point scale.

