#### Secondary outcome for children (based on parents’ assessments)

Effect from the program on the well-being in terms of social and emotional development of the child is expected at T3, T4, and T5.

The child’s social and emotional development is measured at T1, T2, T3, T4, and T5 with the *Ages & Stages Questionnaires – Socio-Emotional Second Edition* (ASQ:SE-2) [26]. It consists of 29–35 questions depending on the age, with 3-point scale response alternatives ranging from “often or always,” “sometimes,” to “seldom or never”. The parent can also indicate whether they worry about the behaviors. The ASQ:SE-2 ends with two open-ended questions.

To assess psychological and behavioral problems in the child, we use parents’ assessments of the *Strengths and Difficulties Questionnaire* (SDQ) [27] at the child age 3 years. The SDQ relates to the child’s behavior over the last 6 months and includes 25 questions that are answered on a 3-point scale with the alternatives “not true at all,” somewhat true,” and “completely true.” The SDQ is only measured at T5.

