## Statistical methods

### Statistical methods for primary and secondary outcomes {20a}

The SPSS and R software will be used for all statistical analyses. Data will be tested for assumptions of parametric statistics. Examinations of pattern and amount of missing data will be performed and if appropriate treated by using relevant estimates. Statistical tests will be two-sided, and the level of significance will be set to 0.05.

Family and infant characteristics will at baseline be summarized overall and by trial arms, with means and standard deviations or medians and ranges for continuous variables. Numbers and percentages will be used for categorical variables. Summarized baseline measures regarding parental strategies and child well-being will also be shown. Any differences between groups at baseline will be examined with *t*-test for independent samples, chi-square test, or Mann–Whitney *U* test.

Fidelity measured as the group leader’s adherence to the program and parents’ participation in *Little ACF* or digital sessions will be summarized with descriptive statistics. Researchers performing statistical analyses of the primary outcome will be blinded to intervention allocation (*Little ACF* or digital session). Measures of effect size will be estimated to assess intervention effects. Hierarchical regression model will be used for assessing primary and secondary outcomes. Linear mixed regression model will be used for continuous data and generalized mixed models for binary and ordinal data. Intervention effects will be assessed for the primary outcome at the post-intervention and at the follow-ups with control for baseline scores. For the secondary outcome, intervention effects will be measured at the follow-ups with control for baseline and post-intervention scores.

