### Methods in analysis to handle protocol non-adherence and any statistical methods to handle missing data {20c}

The results will be analyzed with an intention-to-treat approach and per protocol. Missing data will be analyzed and decisions on imputations for the missing data in the study will be discussed within the research team based on that information.

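### Researcher blinding covers only the primary-outcome analyses, so the plan does not ensure that the child outcomes (ASQ:SE-2 and SDQ) are analysed blind

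*Protocol article*

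**What the plan says.** Three places in the protocol article set the scope of researcher blinding, and they agree.

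- Who will be blinded {17a}: "Researchers are blinded to intervention allocation (Little ACF or digital session) during statistical analyses of the primary outcome".
- Procedure for unblinding {17b}: "Unblinding for researchers will be done in the study after statistical analyses of the primary outcome".
- Statistical methods {20a}: "Researchers performing statistical analyses of the primary outcome will be blinded to intervention allocation".

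The primary outcome is defined on the parent side: "The primary outcome is five aspects of parenting strategies, measured at all five time points of the study (T1, T2, T3, T4, and T5"). The child measures are secondary. For the ASQ:SE-2, "The child’s social and emotional development is measured at T1, T2, T3, T4, and T5". For the other instrument, "The SDQ is only measured at T5".

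On modelling, {20a} states that "Hierarchical regression model will be used for assessing primary and secondary outcomes". It adds that effects on the secondary outcome are assessed at the follow-ups, adjusting for the baseline and post-intervention scores. On missing data, {20c} says that "decisions on imputations for the missing data in the study will be discussed within the research team based on that information".

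**The concern.** Parents and group leaders know the allocation, and every outcome, including the child outcomes, is a parent questionnaire. Analyst blinding cannot remove bias from that source. What it can do is prevent knowledge of the arms from steering the choices still open at the analysis stage: which model, which covariates, how to treat incomplete questionnaires.

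The plan provides this safeguard for the parenting scales and gives no reason for leaving the child outcomes out. As the rule stands, a team could open the code, see the primary result by arm, and only then settle how to analyse the child instruments. At stake is the credibility of the child results, which are the trial's only evidence on child well-being and behaviour problems.

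**Working it through.** No figure in the protocol measures this point, so the check sets the sections side by side.

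1. **Scope of blinding.** Sections {17a}, {17b} and {20a} each name the primary outcome and nothing else. No other section mentions blinding for secondary outcomes.

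2. **Outcomes outside that scope.** The primary outcome covers parental self-efficacy, parent emotion regulation, coping with the child's negative emotions, parenting stress and coparenting. The ASQ:SE-2 and SDQ are the secondary outcomes, and neither is covered.

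3. **Research questions affected.** The Objectives section lists five: parents' emotional regulation, parenting practices, child socio-emotional well-being, child behaviour problems, and engagement and retention in groups. The third and fourth rest on the ASQ:SE-2 and SDQ, the only child measures in Table 2. That is 2 of 5.

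4. **Is the child analysis so fixed that blinding would not matter?** Section {20a} names a model class in advance and adjusts the secondary outcome for T1 and T2 scores.
   - ASQ:SE-2: measured at T1 to T5, so the T1 and T2 scores exist and the adjustment can be applied at T3, T4 and T5.
   - SDQ: measured at T5 only, so neither a T1 nor a T2 score exists and the adjustment cannot be applied as written. Another specification is needed, for example no score adjustment or a different baseline measure as covariate. If the sentence in {20a} is read as meaning the ASQ:SE-2 alone, then no adjustment is stated for the SDQ at all. Either way the choice is open, and nothing places it before unblinding.

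5. **Missing data.** Section {20c} leaves imputation to a team discussion once the missing data have been examined, and does not place that discussion before or after unblinding. The planning assumption shows the choice could matter: 2 × 251 = 502 needed, 502 / 0.75 = 669.3, rounded up to the stated 670, so 0.25 × 670 = 167.5, or about 168 families, are expected to drop out. This is the overall planning figure, not a rate for either child instrument.

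6. **Order of events.** The last measurement of both the primary and the child outcomes is T5. Section {17b} says what must come before unblinding (the primary-outcome analyses) but not whether the child analyses come before or after it. The safeguard is therefore not ensured; the documents do not go so far as to say it is withheld.

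**The case against.** The strongest reply is that the three sections are consistent, that confining analyst blinding to the primary outcome is a disclosed choice, and that detailed model and imputation rules commonly sit in a statistical analysis plan or full protocol not shown here. This stands in part. There is no contradiction among the blinding sections, and the absence of a detailed imputation rule is not the point. What remains is the unblinding rule itself, which the article states and which leaves the child outcomes unprotected.

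Four stronger readings are tempting, and the documents do not support them.

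- *A reader might infer that the child outcomes are certain to be analysed with the arms known.* Section {17b} does not forbid running those analyses before the code is opened. It only fails to require it.
- *A reader might infer that the missing-data method for the child outcomes will be chosen with the arms known.* Section {20c} speaks of the missing data in the study as a whole, and the blinded primary analysis needs that decision too, so it may well be taken blind. What is unsecured is any choice specific to a child outcome that comes later.
- *A reader might infer that unblinding can follow a T2 analysis, leaving about two years of follow-up to be collected with the code open.* The primary outcome is measured through T5, {20a} assesses it at the follow-ups as well as post-intervention, and {21b} plans no interim analyses. Together these make unblinding after T5 the more natural reading. Even under the T2 reading, the ages in the Outcomes section (T2 at about 14–20 months, T5 at 36 months) give 36 − 20 = 16 to 36 − 14 = 22 months, not two years.
- *A reader might infer that analyst blinding is the only protection left.* Randomization is run by the platform with allocation concealed, and an intention-to-treat analysis is planned. Analyst blinding is the only masking described, but not the only safeguard.

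**Conclusion.** The point holds in a limited form. As written, the plan does not ensure a blinded analysis of the ASQ:SE-2 and SDQ, the sole measures for two of the five research questions. Post-unblinding discretion is clearest for the SDQ, because the stated adjustment cannot be carried out for it.

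The possible bias cannot be quantified from the documents. It depends on whether the child analyses are in fact run after the code is opened, and on what an analysis plan not shown may already fix. Neither the sample size nor the validity of the primary analysis is affected. This is an inexpensive improvement to the credibility of the child results, not a flaw that undermines the trial.

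**What to change.** Reword {17a}, {17b} and {20a} so that the arms stay coded (A/B) until the intention-to-treat analyses of all primary and secondary outcomes through T5 have been run and locked. If any results are to be reported before then, lock the models and missing-data rules for every remaining outcome and time point before the first unblinding. In either case, state the SDQ model explicitly, since it has no earlier score to adjust for.

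This needs no extra data, visits or participants. The small cost is that unblinding comes later, or that the analysis code must be locked earlier.

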## Data collection and management

### Plans for assessment and collection of outcomes {18a}

The platform CSAM is used for the collection of data and for study management overall. The platform is familiar to the CHC-nurses and is used in their regular work. All outcome assessments on the parents and the children are made by questionnaires answered by parents. Participating parents are sent links to the questionnaires via the CSAM platform and can answer to the questionnaires electronically on their own smartphone, computer, or tablet. The information is stored on the platform CSAM, downloaded to Excel by the research team, and stored on secure servers at Karolinska Institutet.

The group leader checklists are filled in by hand on paper after each group meeting, and thereafter either scanned and emailed or sent by post to the study coordinator.

### Plans to promote participant retention and complete follow-up {18b}

If a participant has not completed a questionnaire, up to three reminders are sent out if needed. The first one after 3 days, the second one after 10 days, and the last one after 17 days. The group leaders from the municipality or civil society will telephone non-responders after the third automatic reminder.

### Data management {19}

All data are handled in line with the General Data Protection Regulation (GDPR) and procedures of safe handling and storage. The output of the questionnaires including the electronic informed consent of the parents will be stored in the platform CSAM and downloaded to password-protected computers. Access to the data is strictly restricted to the research team. The signed informed consents of the group leaders will be stored in a locked cabinet at the department of global public health at Karolinska Institutet. All research data will be archived for 10 years and thereafter destroyed.

### Confidentiality {27}

The names of the parents and personal identification are replaced by a study ID in the data set. Only the research group has access to the study IDs.

### Plans for collection, laboratory evaluation, and storage of biological specimens for genetic or molecular analysis in this trial/future use {33}

No biological specimens are collected in this study.

## Statistical methods

### Statistical methods for primary and secondary outcomes {20a}

The SPSS and R software will be used for all statistical analyses. Data will be tested for assumptions of parametric statistics. Examinations of pattern and amount of missing data will be performed and if appropriate treated by using relevant estimates. Statistical tests will be two-sided, and the level of significance will be set to 0.05.

Family and infant characteristics will at baseline be summarized overall and by trial arms, with means and standard deviations or medians and ranges for continuous variables. Numbers and percentages will be used for categorical variables. Summarized baseline measures regarding parental strategies and child well-being will also be shown. Any differences between groups at baseline will be examined with *t*-test for independent samples, chi-square test, or Mann–Whitney *U* test.

Fidelity measured as the group leader’s adherence to the program and parents’ participation in *Little ACF* or digital sessions will be summarized with descriptive statistics. Researchers performing statistical analyses of the primary outcome will be blinded to intervention allocation (*Little ACF* or digital session). Measures of effect size will be estimated to assess intervention effects. Hierarchical regression model will be used for assessing primary and secondary outcomes. Linear mixed regression model will be used for continuous data and generalized mixed models for binary and ordinal data. Intervention effects will be assessed for the primary outcome at the post-intervention and at the follow-ups with control for baseline scores. For the secondary outcome, intervention effects will be measured at the follow-ups with control for baseline and post-intervention scores.

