### Outcomes {12}

Data are collected at five time points (Table 2): baseline (T1 – infant age 12–18 months), post-intervention (T2 – infant age about 14–20 months), after 6 months (T3 infant age 18–24 months), after 12 months (T4 – infant age 24–30 months), and in conjunction with the CHC visit when the child is 3 years old (T5). The data are collected through questionnaires to the parents. The baseline questionnaire contains background questions on the age and sex of the child and the parent and questions on parental educational level, country of birth, and family composition as well as several validated instruments that are repeated in the follow-up questionnaires.

**Table 2 Tab2:** Time points for the specific outcome measures and intervention assessments

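### Adjusting the child outcome at follow-up for the T2 score would subtract part of any effect already present at T2, so the arm coefficient need not be the total randomised effect

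*Protocol article*

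**What the plan says.** All places are in the protocol article.

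- **Secondary outcome, Statistical methods {20a}:** "For the secondary outcome, intervention effects will be measured at the follow-ups with control for baseline and post-intervention scores".
- **Primary outcome, same section:** "Intervention effects will be assessed for the primary outcome at the post-intervention and at the follow-ups with control for baseline scores".
- **Timing of T2, Outcomes {12}:** it is the assessment labelled "post-intervention (T2 – infant age about 14–20 months", against 12–18 months at baseline, so about two months later.
- **Timing of randomisation, Implementation {16c}:** it takes place "When twice the number of families needed for a full parental group have completed baseline questionnaires". T1 is therefore the only score taken before allocation.
- **ASQ:SE-2, section on the secondary outcome for children:** "The child’s social and emotional development is measured at T1, T2, T3, T4, and T5". An own T2 score exists, so the rule can be applied as written.
- **Expected timing of the child effect, same section:** an effect on the "social and emotional development of the child is expected at T3, T4, and T5". T2 is not listed.
- **SDQ, same section:** "The SDQ is only measured at T5".

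The article gives no reason for including T2 as a covariate. It states no mediation or direct-effect aim, and no baseline-only analysis of the child outcome.

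**The concern.** Two of the five research questions in Objectives {7} concern the child: socio-emotional well-being and behaviour problems. In a superiority trial of efficacy, the natural target is the difference between randomised arms at T3, T4 and T5, whatever route the effect took.

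A score taken after the programme is itself a possible result of the programme. With that score as a covariate, the arm coefficient compares families who have the same T2 score. Any benefit already visible at T2 and carried forward is then partly credited to the covariate rather than to the arm. A lasting early benefit would be under-reported. An early benefit that fades could appear as harm at follow-up.

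The rule does not name the instrument. The natural reading is the outcome's own T2 score. If the parents' T2 scores were meant, the model would adjust for the parental changes through which the programme is supposed to reach the child, and the objection would be at least as strong.

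**Working it through.** **The plan's own figure.** Sample size {14} gives d = 0.25, two-sided 0.05, 80% power, 251 per arm, 25% drop-out and 670 in total. Check: 2 × (1.960 + 0.842)² / 0.25² = 251.2 per arm, which agrees with 251 apart from rounding; (2 × 251) / 0.75 = 669.3, so 670. These figures are for parental self-efficacy. None is stated for ASQ:SE-2.

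**Inputs for the check.** The following are assumptions, not in the documents: scores standardised within arm and coded so that positive means benefit, a true follow-up effect d_F = 0.25 SD, a T2 effect d_2 of 0, 0.125 or 0.25 SD, and within-arm correlations as shown below. The values 0.25 and 251 per arm are borrowed from the self-efficacy calculation for scale only.

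**Formula.** With arm, T1 and T2 in a linear model:

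- expected arm coefficient = d_F − b2 × d_2
- b2 = (r_2F − r_12 × r_1F) / (1 − r_12²), the slope of follow-up on T2 given T1
- with equal correlations r, b2 = r / (1 + r)

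With T1 only, the expected coefficient is d_F whatever the T2 effect is.

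**Slopes.** r = 0.4: 0.4/1.4 = 0.286. r = 0.6: 0.6/1.6 = 0.375. r = 0.7: 0.7/1.7 = 0.412. Decaying correlations (T1–T2 0.6, T2–follow-up 0.6, T1–follow-up 0.46): (0.6 − 0.276)/0.64 = 0.506.

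**Expected estimate when the truth is 0.25 SD (loss in brackets = b2 × d_2 / 0.25):**

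| Correlations | b2 | d_2 = 0 | d_2 = 0.125 | d_2 = 0.25 |
|---|---|---|---|---|
| equal, 0.4 | 0.286 | 0.250 (0%) | 0.214 (14%) | 0.179 (29%) |
| equal, 0.6 | 0.375 | 0.250 (0%) | 0.203 (19%) | 0.156 (38%) |
| equal, 0.7 | 0.412 | 0.250 (0%) | 0.199 (21%) | 0.147 (41%) |
| decaying | 0.506 | 0.250 (0%) | 0.187 (25%) | 0.123 (51%) |

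A simulation of 1,000,000 records at r = 0.6 gave 0.251, 0.205 and 0.157 for the three T2 effects, in line with the formula.

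**Early effect that fades.** With d_2 = 0.25, d_F = 0 and r = 0.6, the coefficient is 0 − 0.375 × 0.25 = −0.094 (simulation −0.093). This is a spurious effect in the reverse direction.

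**Power, for scale (251 per arm, normal approximation, no clustering).** At r = 0.6 the residual variance is 1 − 0.36 = 0.64 with T1 only, and 1 − (0.6 × 0.375 + 0.6 × 0.375) = 0.55 with T1 and T2.

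- T1 only: SE = √(0.64 × 2/251) = 0.0714; 0.25/0.0714 = 3.50; power 0.94.
- T1 + T2, d_2 = 0.25: SE = √[0.55 × 2/251 × (1 + 0.25²/(4 × 0.64))] = 0.0670; 0.156/0.0670 = 2.33; power about 0.65.
- T1 + T2, d_2 = 0: power 0.965, a small gain over 0.94.

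The same steps, with d_2 = 0.25, take power from 0.86 to 0.62 at r = 0.4 and from 0.975 to 0.70 at r = 0.7.

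**The case against.** The strongest defence is the protocol's own hypothesis. The section on the child outcome expects effects at T3, T4 and T5 and leaves out T2. If parents change first and children later, T2 is a second measurement before the child effect begins, and adjusting for it is harmless and slightly efficient. This stands as far as it goes: with a true T2 effect of zero, the bias is zero. But it is an expectation, not a property of the design. T2 is collected after the programme from parents who know their allocation (Who will be blinded {17a}), and they supply all outcome data (Plans for assessment {18a}). A real early change, or an early change in reporting, is possible. The validity of the main estimate should not depend on its absence.

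Three stronger readings are tempting, and the documents do not support them.

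- **A reader might infer that the model necessarily removes part of the effect.** It does so only if the T2 score has moved.
- **A reader might take a loss of about half as the expected size.** That needs a full 0.25 SD effect already at T2 together with correlations that decay over time. It does not match the protocol's expected timing. Nor are the power figures a loss from any planned power, because the protocol plans none for ASQ:SE-2; they also ignore clustering within families and parent groups.
- **A reader might call the different covariate rules for primary and secondary outcomes a contradiction.** For the primary outcome T2 is itself an assessment point for the effect, so it could not be a covariate there. The rules differ by outcome and do not conflict.

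**Conclusion.** The concern holds in conditional form. As written, the rule makes the T3–T5 arm coefficient for the child outcome the follow-up effect minus b2 times the T2 effect. That equals the total randomised effect only if the programme leaves the T2 score unchanged. No other part of the article supplies a baseline-only estimate or states an aim that would make the T2-adjusted coefficient the intended target.

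The size cannot be fixed from the documents. With an assumed follow-up effect of 0.25 SD, it runs from no loss, through roughly a seventh to a fifth for a T2 effect half as large, to 29–41% for an equal T2 effect under equal correlations. The high end is not the expected case.

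A separate gap in the same sentence is that SDQ has no own T1 or T2 score, so the rule cannot be applied to it using its own scores.

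The point is confined to the secondary outcomes. The primary analysis adjusts for baseline only, and neither it nor the sample size is touched.

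**What to change.** - **ASQ:SE-2:** delete the words *and post-intervention* from the sentence on the secondary outcome, so that the main estimates at T3, T4 and T5 adjust for T1 only.
- **Use of T2:** it may stay as an outcome time point in the mixed model already planned. This is one acceptable form, and its detail can be left to the SAP. Any model with T2 as a covariate should be labelled exploratory.
- **SDQ:** state its covariate rule separately, using only variables measured before randomisation, for example baseline ASQ:SE-2.
- **Timing:** settle this before the T2 results are examined, so that the choice of covariates is not driven by the data.

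The cost is a change of wording; no new data are needed. If the T2 effect is truly zero, some precision is given up: in the r = 0.6 illustration, power of 0.94 instead of 0.965.
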